#### Sample size calculation

We have considered two study designs to inform sample size calculations for the intervention arms.

#### Superiority of ‘same-day initiation’ (arm 2) versus ‘simplified care pathway’ (arm 1)

Acknowledging there are considerable uncertainties around expected uptake of DAAs in both arms, we examined the required sample size in various scenarios of treatment uptake where the intervention (arm 2) would be 5%–10% superior to the simplified care (arm 1). A sample of 700 (350 in each arm) would enable a minimum effect size of 7% favouring arm 2 (presuming 85% uptake in arm 1 simplified care arm) to be detected with 80% power at the 5% significance level. We have assumed 85% treatment initiation based on previous studies that have implemented simplified care pathways in LMIC settings,^17^ accounting for a 15% loss to follow-up prior to treatment initiation. We expect cure rates to be equal across both arms (~95%).

#### Equivalence of ‘same-day initiation’ (arm 2) versus ‘simplified care pathway’ (arm 1)

In the event that we cannot demonstrate superiority of the intervention (arm 2), we have sufficient power with a sample of 700 (350 in each arm) with 1:1 allocation to demonstrate equivalence of the two arms (with equivalence level set at 10%) if uptake in both arms ranges from 75% to 95%.

### Statistical analysis

Primary research question #1: Does the same-day treatment initiation model (arm 2) increase hepatitis C treatment uptake and achievement of SVR (cure) among people who inject drugs compared with the simplified care model (arm 1)?

#### Assessing outcome 1: impact of same-day treatment initiation model on treatment uptake and cure (arm 2 vs arm 1)

The proportion of participants initiating hepatitis C treatment and cured in the simplified care model (arm 1) compared with the same-day treatment care model (arm 2) will be calculated.

The outcome of treatment uptake will be a binary outcome measured by the proportion of participants who are RNA positive and are prescribed treatment and who self-report initiating treatment. The outcome of cure will be measured by the proportion who achieve SRV among those prescribed treatment. Analyses will be conducted using a per-protocol basis, with patients analysed according to the appropriate treatment allocation and study arm following eligibility and exclusion study criteria. Those who are enrolled in arm 2 and later treated via arm 1 study procedures are excluded from primary analyses.

All available binary outcomes will be analysed at the patient level using mixed-effects logistic regression models with random intercepts for clinic and fixed effects for interventions. Models will adjust for covariates, based on any differences in participant characteristics between arm 1 and arm 2 at baseline. These covariates may include: opioid substitution therapy status, injecting frequency, history of incarceration and housing status. ORs and 95% CIs will be reported.

Where data are available, treatment uptake and cure outcomes from arms 1 and 2 will also be compared with available historical data specific to each study country (Armenia, Georgia and Tanzania) and/or globally.

Primary research question #2: What is the feasibility of implementing a decentralised hepatitis C simplified care model (arm 1) and the same-day treatment care model (arm 2) in the varied healthcare settings in the three study countries (Armenia, Georgia and Tanzania)?

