#### Visit 2: confirmatory laboratory results and treatment plan

If the confirmatory laboratory HCV RNA result is negative, the study nurse/doctor will contact the participant (via phone call immediately) and the participant will be asked to stop treatment immediately and to return unused DAAs either directly to the clinic or an outreach worker, or in some cases via a prepaid envelope provided to them in advance. This group of participants will be actively followed up for a face-to-face appointment to ensure they understand the test result and implications and to collect information on their experience of treatment. However, following this next visit, the participant will exit the study. Standard harm reduction messaging and window periods for detection of HCV will be discussed with the participant.If the confirmatory laboratory HCV RNA result is positive, the participant will be assessed for eligibility for treatment continuation based on other laboratory investigations. If a participant is eligible, the participant will continue treatment for a total of 12 weeks.

Participants returning laboratory investigations indicating renal dysfunction, with abnormally high levels of serum creatinine where eGFR <30, will be asked to pause treatment while they seek specialist review and advice on whether to continue treatment.

Participants returning laboratory investigations indicating cirrhosis (FIB-4 score >3.25; ALT or AST >200 U/L; bilirubin >1.14 mg/dL; albumin <3.5 g/dL without other obvious cause) will be discussed with supervising specialist for a decision regarding pausing treatment or organising a specialist referral for review without pausing treatment.

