### Sample size

The primary study aim (aim 1) is to assess if same-day treatment initiation model (arm 2) increases hepatitis C treatment uptake and achievement of SVR, compared with a simplified care model (arm 1). The study is powered to measure the primary outcomes of treatment uptake and cure in arm 1 and arm 2 in a pooled analysis of all three countries. In addition, we will compare retention in care between arm 1 and arm 2, in each country individually. The sample size is presented below (table 3).

**Table 3 T3:** Country and site enrolment and treatment targets

Country	Site	Target enrolment	Target DAA initiation arm 1	Target DAA initiation arm 2
Armenia	Yerevan, National Center for Infectious Diseases	500	58	58
	Shirak, Gyumri Medical Center	164	19	19
	Lori, Vanadzor Medical Center	163	19	19
	Syunik, Kapan Medical Center	163	19	19
	**Total (Armenia**)	**990**	**115**	**115**
Georgia	Tbilisi, Hepa plus	1100	18	18
	Rustavi, New Vector	360	12	12
	Gori, Step to Future	440	42	42
	Xenon	1200	48	48
	**Total (Georgia**)	**3100**	**120**	**120**
Tanzania	Dar es Salaam, Mukikute	522	60	60
	Dar es Salaam, Temeke Regional Referral Hospital MAT Clinic	478	55	55
	**Total (Tanzania**)	**1000**	**115**	**115**
**Total**		**5090**	**350**	**350**

* Sample sizes based on the following antibody and RNA prevalence estimates: Armenia: 39% HCV Ab prevalence, 75% HCV RNA prevalence. Georgia: 58% HCV Ab prevalence, 30% HCV RNA prevalence. Tanzania: 40% HCV Ab prevalence, 75% HCV RNA prevalence.

Ab, antibody; DAA, direct-acting antiviral; HCV, hepatitis C virus.

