#### Assessing secondary outcomes

##### Impact of same-day treatment initiation model on treatment completion and cure

Participants will be classified as completing treatment if they self-report that they have taken at least 8 weeks of treatment, with <14 days missed doses. Proportion completing treatment will be assessed among those who were confirmed RNA positive. The proportion of participants who complete hepatitis C treatment will be compared between arms. We will also assess treatment completion based on completion of the full 12-week treatment course.

The proportion of participants who achieve SVR (4–20 weeks post-treatment completion) among those who were confirmed RNA positive and initiated hepatitis C treatment in the simplified care model (arm 1) will be compared with the same-day treatment care model (arm 2), using per-protocol analysis of those allocated to each arm.

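### The primary cure denominator, as written, includes RNA-negative people in arm 2 only, and the claim of power for cure has no calculation behind it

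*Protocol article*

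**What the plan says.** All references are to the protocol article.

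- **Primary cure** (Assessing outcome 1): "The outcome of cure will be measured by the proportion who achieve SRV among those prescribed treatment". The sentence just before it defines uptake as "measured by the proportion of participants who are RNA positive and are prescribed treatment and who self-report initiating treatment".
- **Analysis set** (same section): "Analyses will be conducted using a per-protocol basis, with patients analysed according to the appropriate treatment allocation and study arm". One exclusion is named: "Those who are enrolled in arm 2 and later treated via arm 1 study procedures are excluded from primary analyses".
- **Arm 1, Visit 2:** only participants with a positive confirmatory RNA result go on to be assessed for treatment.
- **Arm 2, Visit 1:** treatment is offered on the 5 min antibody result, before RNA is known.
- **Arm 2, Visit 2:** RNA-negative participants are told to stop and are seen once more. Then: "However, following this next visit, the participant will exit the study".
- **Proportion overtreated:** this group is described as having been prescribed or having started treatment before a negative RNA result.
- **Secondary SVR comparison:** its denominator is "among those who were confirmed RNA positive and initiated hepatitis C treatment in the simplified care model (arm 1") and the same in arm 2.
- **Sample size:** "The study is powered to measure the primary outcomes of treatment uptake and cure in arm 1 and arm 2". The superiority subsection then says "We expect cure rates to be equal across both arms (~95"%).

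**The concern.** Being prescribed treatment means different things in the two arms. In arm 1 it implies RNA positivity. In arm 2 it implies a reactive 5 min test, and the plan itself expects some of those people to be RNA negative. They have nothing to cure and leave before SVR assessment, so they can enter the denominator but never the numerator. The named exclusion does not remove them: it covers arm 2 enrolees treated through arm 1 procedures, who are a different group. A primary outcome computed as written would show a deficit in arm 2 that comes from the definition and not from the care model.

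Research question 1 asks whether arm 2 increases both uptake and achievement of SVR. The secondary denominator (RNA positive and started) removes the artefact, but it conditions on starting treatment, which is the step that arm 2 is meant to change. On its own it does not show whether more infected people end up cured.

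The power statement is a separate matter. The sample size section names cure alongside uptake, but both subsections that follow calculate for uptake alone.

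**Working it through.** **Inputs.** Arm 2 treatment-start targets are 115 (Armenia), 120 (Georgia) and 115 (Tanzania), from Table 3. RNA prevalence is 75%, 30% and 75%, from the Table 3 footnote, read here as the RNA-positive share of antibody-positives. Cure is 95%; arm 1 uptake is 85% and the difference is 7 points, so arm 2 uptake is 92% (superiority subsection). The equivalence margin is 10 points (equivalence subsection). Two-sided 5% tests are assumed, because sidedness is not stated.

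**The plan's own figure.** For 85% versus 92% with 80% power, the two-proportion formula gives 325 per arm without continuity correction and 353 with it. At 350 per arm, power is 82.9% and 79.7% respectively. The stated 350 for uptake is reproduced.

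**Apparent cure under the literal denominator.** Let r be the RNA-positive share of antibody-positives, and f the share of RNA-negative antibody-positives who react by 5 min. All RNA-positives are assumed to react by then. The RNA-positive share of arm 2 starters is r / (r + (1 − r)f).

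- f = 1: 115×0.75 + 120×0.30 + 115×0.75 = 208.5 of 350 (59.6%). Apparent cure is 0.596 × 0.95 = 57%.
- f = 0.5: the shares are 0.75/0.875 = 0.857, 0.30/0.65 = 0.462 and 0.857. This gives 98.6 + 55.4 + 98.6 = 252.5 of 350. Apparent cure is 69%.
- f = 0.1: 319.9 of 350. Apparent cure is 87%.
- Arm 1: 95% in every case.

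These figures let the 350 count every arm 2 start. If it counts RNA-positive starts only, f = 1 means 115/0.75 + 120/0.30 + 115/0.75 = 707 people prescribed, and apparent cure is 0.95 × 350/707 = 47%.

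**How small a share matters.** An RNA-negative share of 0.10/0.95 = 10.5% opens a 10-point gap by itself. At a 10% share, apparent arm 2 cure is 0.90 × 0.95 = 85.5%. With 350 per arm, the chance of a significant result against arm 2 is then 99%, and the power to show equivalence at 10 points is 8%.

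**Cure among RNA-positive starters, 95% in both arms.** Equal rates leave no superiority power: a two-sided test rejects 5% of the time, half of that in favour of arm 2. Equivalence at 10 points (two one-sided tests at 5%, normal approximation) has over 99.9% power at 350 per arm, and 99.97% if only 209 arm 2 starters are RNA positive.

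**SVR among all RNA-positives.** The plan's assumptions give 0.85 × 0.95 = 80.8% versus 0.92 × 0.95 = 87.4%, taking every starter to be tested for SVR.

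- 350 RNA-positives per arm: power 67%.
- If the arm 2 target counts RNA-negative starts and f = 1: arm 1 has 350/0.85 = 412 RNA-positives and arm 2 has 208.5/0.92 = 227. Power is 58%. On the same numbers, power for uptake is 74%.

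**The case against.** The strongest reply is that the literal reading is not what was meant. The preceding sentence on uptake refers to RNA-positive people who are prescribed treatment, and the cure sentence may lean on it. Equal cure of about 95% is attainable in arm 2 only among RNA-positive people. The secondary SVR comparison is restricted to them, and RNA-negative starters have their own overtreatment outcome. This makes an RNA-positive intention plausible. It does not settle the matter, because the cure sentence and the named exclusion are the stated rule, and neither carries the restriction.

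A secondary denominator may also legitimately differ from a primary one, and SVR among RNA-positive starters is a sound measure of treatment success. Uptake and a descriptive care cascade are reported beside it. That stands; the gap is only that no stated comparison gives SVR among all infected participants by arm.

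On power, a reader might infer that the faulty denominator is what removes power for cure, or that no useful power for cure is possible. The documents support neither inference. Superiority power is absent because the plan assumes equal cure among starters. Equivalence among RNA-positive starters would be very well powered. The plan simply does not state that hypothesis for cure, since its equivalence range is given for uptake.

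Finally, the 62% positive predictive value quoted in the Introduction would give 0.62 × 0.95 = 59%. It should not be carried over directly, because the Introduction says that accuracy improves when previously treated people are excluded, as they are here.

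**Conclusion.** The concern holds in two separate parts.

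**Denominator.** As written, primary cure is not comparable between arms. On the plan's own rates, arm 2 would show about 57% to 69% against 95% as f falls from 1 to 0.5, and it would approach 95% only if almost no RNA-negative people react by 5 min. The size rests on reading the Table 3 RNA rates as conditional on antibody positivity, on an f that the documents do not give, and on the 350 counting all arm 2 starts. It also arises only if the sentence is applied literally. A reader should not conclude that the trial will report such a deficit, only that the stated rule would produce one.

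**Power.** The claim for cure is unsupported as it stands, because no cure hypothesis or calculation accompanies it. A single replacement figure would be equally unsupported: the plan does not say whether the arm 2 target counts RNA-negative starts, and power for SVR among all RNA-positives runs from about 58% to 67% accordingly.

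**What to change.** 1. In Assessing outcome 1, restrict the primary cure denominator to participants with confirmed positive baseline RNA in both arms. Keep the stated exclusion of arm 2 enrolees treated through arm 1 procedures, unless a change is justified.
2. To answer research question 1, report SVR among all RNA-positive participants by arm, alongside SVR among RNA-positive starters.
3. In the Sample size section, either state the cure hypothesis (for example, equivalence at 10 points among RNA-positive starters, with over 99.9% power at 95% cure) or withdraw the cure power claim.
4. State whether the arm 2 target of 350 counts RNA-negative starts. Until that is settled, quote any power for SVR among all RNA-positives (80.8% versus 87.4%) as a range: about 67% with 350 per arm, about 58% with about 412 versus 227.

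The cost is wording only. Baseline RNA is already collected from antibody-positive participants in both arms. The stated power for cure becomes less favourable.

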#### Arm 1 study procedures

##### Visit 1: enrolment, laboratory investigations, physical examination and medical history taking

Eligible participants enrolled in the study will have a OraQuick rapid hepatitis C antibody test using a fingerstick specimen, according to the manufacturer’s instructions, with the result documented at 20 minutes. In addition, the OraQuick rapid test result for the first 5 min will be documented at 1 min intervals, including with a photograph to record whether the test is reactive or non-reactive at that time point. The exact time at which the test first turns reactive will also be recorded. The result at 20 min will be provided to the participant. If the antibody result is negative, confirmatory testing will not be offered and the participant will exit the study with no further investigations performed. If the antibody result is positive, blood samples will be collected for confirmatory laboratory RNA testing and additional pretreatment investigations including complete blood count (platelets, haemoglobin), liver function tests (alanine aminotransferase (ALT), aspartate aminotransferase (AST), albumin, bilirubin) and renal function tests (serum creatinine±estimated glomerular filtration rate (eGFR)). The FIB-4 score will be calculated and used to determine cirrhosis status.

In addition, additional rapid tests will be conducted at baseline visit:

HIV antibody 1/2 RDT using venous blood sample.Hepatitis B surface antigen (HBsAg) RDT using venous blood sample.Urine dip-stick pregnancy test for all female participants with childbearing potential aged 18–49 years (pregnancy test can also be completed as part of pretreatment laboratory investigations in arm 1).

The brands of HIV and HBsAg RDTs will be included in online supplemental material 1; brands differ by country, depending on national procurement.

In Tanzania and Armenia, those who return a non-reactive HBsAg RDT and have no evidence of prior hepatitis B vaccination will be offered vaccination through the study. Evidence of vaccination is sourced through medical records accessible by study sites. In Georgia, those eligible for vaccination will be referred to a newly established national programme for vaccination.

Those newly diagnosed with HIV will be referred to treatment and be allowed to represent for study participation once their HIV is clinically stable, if recruitment is still open at that time in Armenia and Tanzania.

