If the specialist determines that the participant does not have decompensated cirrhosis, then they can receive DAA treatment as part of the study in arm 1 and will be followed up according to study timelines.

If the participant has elevated serum creatinine, the study doctor should calculate the eGFR. If eGFR is <30 mL/min/1.73 m^2^, they will be excluded from receiving DAA therapy as part of the study and referred for specialist review for ongoing care.

If the participant is deemed eligible for treatment, the study doctor will provide them with the first 4 weeks of SOF/VEL (28-day bottle) and ask them to begin treatment.

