### Arm 2 study procedures

#### Visit 1: enrolment, laboratory investigations, physical examination, medical history taking, drug-drug interactions review and presumptive treatment prescription

Eligible participants enrolled in arm 2 will undergo an OraQuick rapid hepatitis C antibody test using a fingerstick specimen as per arm 1. The result at 5 min will be provided to the participant as a preliminary result and used to inform whether same-day treatment is offered. This is the key difference between arm 1 and arm 2, with participants in arm 2 offered presumptive treatment based on this result at 5 min, without waiting for the RNA result.

Laboratory testing on a venous sample is then required to confirm whether the participant has current infection. If the antibody result is negative, confirmatory testing will not be offered and the participant will exit the study with no further investigations performed (as per arm 1).

If the antibody result is positive, blood samples will be collected for confirmatory laboratory RNA testing and additional investigations (as per arm 1). The FIB-4 score will be calculated and used to determine cirrhosis status.

If the POC result is positive at 5 min, blood samples will be collected for confirmatory laboratory RNA testing and additional investigations. Additional rapid tests, including HIV antibody 1/2 RDT, HBsAg RDT, rapid urine pregnancy tests, physical examination for signs and symptoms of decompensated cirrhosis, medical history taking and drug-drug interactions chart review for contraindications for same-day treatment will be conducted. Any participants with suspected decompensated cirrhosis or other comorbidity that may exclude participants from treatment in arm 2 of this study will be referred to a specialist for further review and care.If the POC result is a negative antibody test at 5 min and a positive test at 20 min, blood samples will be collected for confirmatory laboratory RNA testing and additional investigations, and the participant will be told that their test indicates they have been exposed to hepatitis C but may have a current infection. These participants are ineligible for same-day treatment in arm 2, but if their RNA test is subsequently positive, they will be offered treatment as per study procedures of arm 1 of the study but will not count towards the enrolment target.

Participants will be eligible for same-day treatment if they have:

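### The primary analysis removes arm 2 participants who are treated by the arm 1 route but keeps their arm 1 counterparts, so uptake is not compared in like populations; the documented effect is small and its direction is left open

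*Protocol article*

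**What the plan says.** Under Statistical analysis, Assessing outcome 1, the article states: "Analyses will be conducted using a per-protocol basis". It then adds: "Those who are enrolled in arm 2 and later treated via arm 1 study procedures are excluded from primary analyses". No matching rule is given for arm 1. The uptake outcome is being RNA positive, prescribed treatment and reporting that treatment was started.

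The arm 2 Visit 1 section identifies a group that the rule catches. "If the POC result is a negative antibody test at 5 min and a positive test at 20 min, blood samples will be collected" for RNA testing, and then: "These participants are ineligible for same-day treatment in arm 2, but if their RNA test is subsequently positive, they will be offered treatment" by the arm 1 procedures, "but will not count towards the enrolment target".

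In arm 1 the reading that governs care is the later one: "The result at 20 min will be provided to the participant". The arm 1 Visit 1 section also has the test read and photographed each minute up to 5 min, so the 5 min status of arm 1 participants is known.

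Laboratory results come into play at different moments. In arm 1, of people with eGFR below 30, Visit 2 says "they will be excluded from receiving DAA therapy as part of the study". In arm 2 the same result arrives after the first bottle may have been dispensed, and the person "will be asked to pause treatment while they seek specialist review".

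**The concern.** Research question 1 asks whether the same-day model raises uptake. The exclusion acts in one arm only and rests on information that arises after enrolment: the 5 min reading, the RNA result and being treated. The arm 2 estimate then describes RNA-positive people who were positive at 5 min. The arm 1 estimate describes RNA-positive people who were positive at 20 min. These are different populations, and the people who differ are those the same-day model missed.

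The sentence can also be read in two ways. Taken literally, it removes people because they were treated, which selects on the outcome and discards uptake successes from arm 2. Taken as removing everyone diverted to the arm 1 route, started or not, it takes out people who may be harder to start. The two readings push the estimate in opposite directions, and the definition of a primary analysis set should not leave that open.

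**Working it through.** **The plan's own figure.** Inputs from Sample size calculation: 85% against 92%, 80% power, 5% significance (taken as two-sided), 350 per arm.

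- Without continuity correction: n = [1.96·√(2·0.885·0.115) + 0.8416·√(0.85·0.15 + 0.92·0.08)]² / 0.07² = 325 per arm.
- With continuity correction: 353 per arm. Power at 350 per arm is 79.7%.

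The stated 350 is reproduced, so 7 points is the yardstick.

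**Size of the named group.** Background and rationale cites a 5 min sensitivity for viraemia of 100% (95% CI 98.4% to 100%). The share f of RNA-positive people who are negative at 5 min is therefore 0 to 1.6%. At the upper end this is 0.016 × 350 = 5.6 people per 350.

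**Bias formulas.** Let u_ex be uptake in the diverted group and u_rest uptake in the others, set at 92% (the design value for arm 2). True arm 2 uptake is (1−f)·u_rest + f·u_ex.

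- Whole group removed: bias = f·(u_rest − u_ex).
- Only the treated removed (literal wording): bias = (1−f)·u_rest / (1 − f·u_ex) − [(1−f)·u_rest + f·u_ex].

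Results at f = 1.6%, in percentage points:

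| u_ex | Whole group removed | Only treated removed |
|---|---|---|
| 0% | +1.47 | 0.00 |
| 50% | +0.67 | −0.07 |
| 70% | +0.35 | −0.09 |
| 85% | +0.11 | −0.11 |
| 100% | −0.13 | −0.13 |

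At f = 0 both biases are zero.

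**Effect on a false claim.** Suppose true uptake is 85% in both arms, 350 per arm, and the whole group is removed at f = 1.6%. Apparent arm 2 uptake becomes (0.85 − 0.016·u_ex)/0.984: 85.2%, 85.6% or 86.4% for u_ex of 70%, 50% or 0%. The chance of a significant result favouring arm 2 rises from 2.5% to 3.1%, 4.0% or 7.5%.

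**What a larger bias would need.** With whole-group removal, 7 points requires f = 0.07/(0.92 − u_ex): 7.6% at zero uptake, 16.7% at 50%, 31.8% at 70%. This could only come from also removing people who cannot start the same day because of interactions, comorbidity or physical signs. Their share is not given. Assuming x = 10 to 15% of RNA-positives with uptake u = 50 to 70%, and 85% overall in both arms, arm 2 after removal shows (0.85 − x·u)/(1 − x):

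- x = 10%, u = 70%: 86.7%, a spurious gain of 1.7 points.
- x = 10%, u = 50%: 88.9%, 3.9 points.
- x = 15%, u = 60%: 89.4%, 4.4 points.
- x = 15%, u = 50%: 91.2%, 6.2 points.

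On the literal reading with u = 60%, (0.85 − x·u)/(1 − x·u) gives 84.0% (x = 10%) and 83.5% (x = 15%), a loss of about 1.0 and 1.5 points.

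**The case against.** The strongest reply is about size. Only the group negative at 5 min and positive at 20 min is expressly sent to the arm 1 procedures, and the article's own sensitivity figure makes it very small, possibly empty. Taken word for word, the rule works slightly against arm 2 and so is conservative for superiority. This stands, and it rules out any claim that the rule has been shown to produce a bias as large as the target effect.

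A reader might infer that everyone unable to start the same day is also treated by the arm 1 route and removed. The arm 2 Visit 1 section does not say so: it refers suspected decompensation or an excluding comorbidity to a specialist. Participant eligibility also lists significant comorbidity and inability to stop contraindicated medicines as exclusions for the whole study, so the counterparts in arm 1 may drop out too.

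A reader might likewise infer that arm 2 participants who start and then return a disqualifying laboratory result count as uptake while their arm 1 counterparts do not. The outcome definition allows that. However, the per-protocol set is to follow the study's eligibility and exclusion criteria, which may remove them. On both points the documents show unclear counting, not a stated asymmetry.

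It can also be said that there is no randomisation to preserve, that per-protocol sets are customary for the fallback equivalence claim, and that the care cascade and accuracy results will help to show 5 min misses. These weaken the general case against per-protocol. They do not justify an exclusion applied in one arm only, since consecutive enrolment still gives each participant a definite arm. Nor is the rule a detail left to the analysis plan, because the article states it.

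**Conclusion.** The concern holds in limited form and should be fixed. The stated primary set is not comparable between arms, because people whom the arm 2 model misses leave arm 2 while their counterparts stay in arm 1.

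For the group the article names, the effect ranges from about −0.1 points (only the treated removed) to between 0 and about +1.5 points (whole group removed, with uptake in it no higher than in the rest). The upper figure is about one fifth of the 7-point design effect and assumes that none of the group starts treatment.

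These limits rest on a sensitivity from Canadian and Spanish cohorts. The trial measures that same sensitivity as a secondary outcome, so its primary analysis should not depend on the value being near 100%. The range of 1.7 to 6.2 points depends on an assumed 10 to 15% share with 50 to 70% uptake, and on a reading that the documents do not state. It shows why the handling of people who cannot start the same day needs to be written down, and is not an estimate of the bias in this trial.

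**What to change.** Define the primary set for uptake as all enrolled participants with a positive baseline RNA result, analysed by arm of enrolment. Participants enrolled in arm 2 and treated by the arm 1 procedures stay in arm 2, and those who start count as having started.

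State how people who cannot start the same day, and those with disqualifying laboratory results, are counted. If eligibility is used to restrict the set, apply it from Visit 1 data, including the laboratory results from that sample, identically in both arms. This concerns counting only and changes nothing in clinical management.

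Keep the per-protocol set as a sensitivity analysis, restricted to 5 min positives in both arms. Report both sets for the fallback equivalence claim.

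The cost is rewording. RNA and baseline bloods are already taken from everyone reactive at 20 min in both arms, and the 5 min reading is recorded in arm 1. No visit or sample is added. The downside is that the arm 2 estimate may be slightly less favourable.
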